
### Primary outcomes

#### Feasibility

Feasibility of the intervention will be determined by the number of eligible patients recruited, retention and adherence rates to the exercise programme. The retention rate will be defined as the percentage of individuals who completed the PEPA Trial. Adherence will be defined as the percentage of exercise sessions attended by those who were randomised to the intervention group. Adherence to the exercise programme will be recorded using attendance records (recorded by the study physiotherapist)/participant exercise diaries (recorded by the participant).

#### Acceptability

The acceptability of the exercise programme will be assessed by a semi-structured questionnaire administered at pre hospital discharge.

### Secondary outcomes

Secondary outcomes will include complication rates, length of hospital stay, functional capacity (assessed with the 6MWT), physical activity (assessed with the IPAQ-SF), quadriceps strength (assessed with the Isometric Quadriceps Strength Assessment and the Five Times Sit to Stand Test) and quality of life (assessed with the SF36-v2®). Other outcomes, such as adverse events (defined as any undesirable event such as injury, falls, discomfort, or pain), will be collected throughout the trial. Questions related to participants views and satisfaction with the exercise programme will be asked at the end of the study (pre discharge).

### Blinding

Research officers involved in data collection will be blinded to group allocation. Due to the nature of the intervention, it will not be possible to blind participants and the physiotherapist delivering the pre-operative exercise intervention. However, the physiotherapist conducting the physical assessments in both groups and the surgeon will be blinded to participant group allocation and participants will be asked not to disclose group allocation to their physiotherapist assessor and surgeon. In addition, the statistician performing the statistical analyses will be blinded to group allocation.

### Statistical analysis

All data will be stored in a Research Electronic Data Capture (REDCap) database and statistical analyses will be performed using IBM SPSS Statistics version 22 (SPSS Inc., Chicago, IL, USA).

The proportion of patients who consent to the study and the reasons for non-consent will be summarised. Characteristics of patients randomised to each group will be compared. The number and percentage of intervention-group participants who commenced, completed each component and completed the full exercise programme will be calculated. The proportion of patients who developed major complications and the median length of stay will be compared between the intervention and control groups. For the secondary outcomes (functional capacity, physical activity, quadriceps strength and quality of life) change in scores between baseline, 1 week pre-operatively, 10 days in hospital and pre hospital discharge will be compared between the intervention and control groups to inform future sample size calculations. The overall score of the semi-structured questionnaire will reveal the acceptability of the exercise programme.

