Therefore, the *primary aims* of this pilot randomised controlled trial are to determine: (1) the feasibility of incorporating a standardised, intensive exercise programme into the pre-operative period for patients undergoing cytoreductive surgery or pelvic exenteration at Royal Prince Alfred Hospital (RPAH), Sydney; (2) the acceptability of the exercise programme to patients and (3) the acceptability to patients of being randomised to the exercise programme or usual care. The *secondary aim* is to obtain pilot data on the likely difference in key outcomes (post-operative complications, length of hospital stay, post-operative functional capacity and quality of life) to inform the sample size calculation for the substantive randomised clinical trial.

Our hypothesis is that the pre-operative exercise programme in combination with usual care is feasible and acceptable for patients undergoing cytoreductive surgery and pelvic exenteration.

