**Fig. 2 Fig2:**
[figure not shown]
Details of the schedule of enrolment, interventions and assessments according to the Standard Protocol Items: Recommendations for Intervention Trials (SPIRIT) Diagram

A total of 20 patients will be randomly assigned via concealed allocation to receive: (1) a pre-operative exercise programme and usual care (intervention group) or (2) usual care alone (control group). To reduce participant burden, this study will use clinical data collected by the Pelvic Exenteration Surgery Quality and Improvement (PESQI) (Protocol No X13–0283 and HERC/13/RPAH/371) and the Peritonectomy Surgical Research Programme (PREMIER) (Protocol No X16–0482 and HREC/16/RPAH/691). Ethical approval for the PEPA Trial was obtained by the Sydney Local Health District Human Research Ethics Committee (Protocol No X17–0189 and HREC/17/RPAH282).

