### Randomisation and allocation concealment

A research officer not involved in the trial will prepare the group allocation after written informed consent and baseline assessment are obtained. Randomisation will be carried out on a 1:1 basis and will utilise a computer-based, random-sequence generator, stratified by surgical procedure (cytoreductive surgery or pelvic exenteration). Consecutively numbered, sealed, opaque envelopes containing group allocation will be prepared by a researcher officer not involved in the trial. The concealed envelopes will be stored in a locked cabinet and will be opened in sequence to reveal group allocation by a research officer not involved in the recruitment process, treatment, or assessment of outcomes.

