### Outcome measures

The PEPA Trial will collect the following information (Fig. 2):Demographic and clinical characteristics: prior to surgery (baseline), patients’ height and weight (kg), date of birth, gender, address, and type of cancer will be obtained from the PESQI and PREMIER databasesPhysical assessment: the physical assessment will be performed by the study physiotherapist and will be collected at baseline, within a week before the surgery, 10 days post-operative and pre hospital discharge. The following outcomes will be assessed:*International Physical Activity Questionnaire-Short Form (IPAQ-SF)*: self-reported physical activity will be measured using the IPAQ-SF [30]. The IPAQ-SF will be used to calculate the metabolic equivalent (MET) minutes per week spent in walking, in moderate and vigorous activities and the total MET minutes per week. The amount (minutes per day and number of days per week) of walking, moderate activity and vigorous activity recorded by the IPAQ-SF will be multiplied by a weighting (3.3 for walking, 4 for moderate activity and 8 for vigorous activity) to calculate MET minutes per week in each activity, and these values will be summed to produce the total MET minutes per week. Sedentary behaviour will be determined based on time spent sitting per day (minutes). In addition, participants will be categorised as achieving a low, moderate, or high physical activity level*Six-minute Walk Test (6MWT)*: the 6MWT will be conducted in accordance with the protocol of the American Thoracic Society. Participants will be instructed to walk as quickly as possible for 6 min up and down a 30-m, straight, indoor corridor. Standardised encouragement will be given each minute during the test. Oxygen saturation, heart rate and the distance walked will be recorded [31]*Isometric Quadriceps Strength Assessment*: quadriceps strength will be measured using a hand-held dynamometer [32]. Patients will be assessed in a sitting position with the knees and hips at 90°. Maximal voluntary contraction force (reported in kilograms) will be assessed as the best of three reproducible manoeuvres*Five Times Sit to Stand Test*: lower-limb strength and function will be measured using the Five Times Sit to Stand Test [33]. Patients will sit with arms folded across the chest and with their back against a chair. Patients will be instructed to stand up and sit down five times as quickly as possible. Time taken to complete the test will be recorded by the physiotherapist*Cardiopulmonary Exercise Test (CPET)*: the CPET will be conducted using a computer-controlled, electromagnetically braked cycle ergometer (Ergoline VIAsprint 200P, Germany) in accordance with the American Thoracic Society/American College of Chest Physicians (ATS/ACCP) statement [34]. maximal oxygen uptake (VO_2_ max; ml/kg/min) and anaerobic threshold (ml/kg/min) will be recorded at baseline and within a week before the surgery3.Clinical outcomes: clinical outcomes will be collected intra-operatively and post-operatively from PESQI and PREMIER databasesComplication rates: will be defined as the total number of complications post-operative and will be reported according to the Clavien-Dindo classification of surgical complications [35]Length of hospital stay: will be defined as the duration of inpatient hospital stay with the day of surgery considered as day 04.Quality of life, the Exercise Self-Efficacy Scale, the Depression, Anxiety, Stress Scale, and Participants views and satisfaction: quality of life will be measured by the Short Form 36 version 2 (SF-36v2®, Australian English) [36] at baseline, within a week before the surgery, 10 days post-operative and at pre hospital discharge. Exercise self-efficacy (measured with the Exercise Self-efficacy Scale) [37] and depression, anxiety, stress (measured with the Depression, Anxiety, Stress Scale) [38] will be assessed at baseline. Participants’ views and satisfaction with the study intervention will be assessed at pre hospital discharge

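### The continuous secondary outcomes are to be compared as change scores, with neither baseline nor surgical procedure named as a covariate; ANCOVA would usually be more precise and give better inputs for the next trial

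*Protocol article*

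**What the plan says.** The Statistical analysis section treats quality of life, quadriceps strength, physical activity and functional capacity together. For these, "change in scores between baseline, 1 week pre-operatively, 10 days in hospital and pre hospital discharge will be compared between" arms, and the same sentence gives the purpose as feeding the sample size of a later trial. I read this as change from baseline to each later time. The section names no test, model or covariate for the comparison.

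Two relevant variables are available by design:

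- **Baseline.** Under Outcome measures, the physical assessment "will be collected at baseline, within a week before the surgery, 10 days post-operative and pre hospital discharge", and the SF-36v2 follows the same schedule. Under Randomisation and allocation concealment, allocation comes after the baseline assessment, so baseline is a true pre-randomisation covariate.
- **Procedure.** Randomisation is "stratified by surgical procedure (cytoreductive surgery or pelvic exenteration".

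The end of the Background makes pilot data for the definitive sample size the secondary aim. The key outcomes listed there include functional capacity and quality of life, as well as complications and length of stay.

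**The concern.** The section does more than leave the model open: it chooses the quantity to be compared, and that quantity is change. Subtracting the baseline in full is the best use of it only when correlation with follow-up is very high. Two of the three follow-ups (10 days after surgery and before discharge) come after cytoreductive surgery or pelvic exenteration, while baseline is taken 2 to 6 weeks before the operation. A low to moderate correlation is plausible there. It may be higher for the assessment one week before surgery, since no operation intervenes.

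Two things are at stake. With about 10 patients per arm, the pilot's between-group estimates would be less precise than the same data allow, and a chance baseline difference would carry into them. In addition, the SD of change is the natural by-product of the stated comparison. It is the wrong input if the later trial uses a baseline-adjusted analysis.

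**Working it through.** **The plan's own figure.** "A total of 20 patients will be randomly assigned via concealed allocation", and "Randomisation will be carried out on a 1:1 basis", so about 10 per arm. No alpha, power, SD or effect size accompanies the 20, so it cannot be re-derived statistically. The only arithmetic attached to it is recruitment: 20 / 3 per month = 6.67, hence the 7 months given under Timeline.

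**Assumptions.** The baseline/follow-up correlation rho is not given, so 0.3 to 0.9 is used. The SD is taken as equal at both times.

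**Step 1, precision.** In units of SD²:

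- Variance of change = 2(1 − rho)
- ANCOVA residual variance = 1 − rho²
- Ratio = 2(1 − rho) / [(1 − rho)(1 + rho)] = 2/(1 + rho)

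**Step 2, cost of estimating the slope at N = 20.** With one covariate, the ANCOVA variance grows by (N − 3)/(N − 4) = 17/16 = 1.06. Simulation (20,000 runs per rho, 10 per arm, baseline as the only covariate) gives the ratios in the table. Adding procedure costs one further degree of freedom.

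**Step 3, illustrative definitive trial.** With an assumed effect of 0.5 SD, two-sided 5% and 80% power, n per arm = 2(1.960 + 0.842)² V / 0.5² ≈ 62.8 V, where V is the variance from Step 1, rounded up.

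| rho | Change variance | ANCOVA variance | Ratio | Simulated ratio, N = 20 | n per arm, change | n per arm, ANCOVA |
|---|---|---|---|---|---|---|
| 0.3 | 1.40 | 0.91 | 1.54 | 1.45 | 88 | 58 |
| 0.5 | 1.00 | 0.75 | 1.33 | 1.26 | 63 | 48 |
| 0.7 | 0.60 | 0.51 | 1.18 | 1.12 | 38 | 33 |
| 0.9 | 0.20 | 0.19 | 1.05 | 0.99 | 13 | 12 |

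The follow-up value alone has variance 1. Change is therefore worse than ignoring baseline when 2(1 − rho) > 1, that is, when rho < 0.5.

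**Step 4, chance imbalance.** The difference in baseline means has standard deviation sqrt(2/10) = 0.45 SD. Given an observed difference D, the change-score contrast is shifted by −(1 − rho)D. At rho = 0.5 and D = 0.45 SD, the shift has size 0.5 × 0.45 ≈ 0.22 SD.

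**Step 5, how well a pilot variance is known.** With 18 degrees of freedom, the 95% interval for the true variance runs from 0.57 to 2.19 times the estimate. With 16, as left by a model with treatment, baseline and procedure, it runs from 0.55 to 2.32 times.

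**Step 6, unequal SDs.** With k = baseline SD / follow-up SD, the ratio is (1 + k² − 2·rho·k)/(1 − rho²). At rho = 0.5:

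- k = 0.7: 0.79/0.75 = 1.05
- k = 1.3: 1.39/0.75 = 1.85

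**Stratum.** The gain from adjusting for procedure cannot be computed, because no between-procedure variance is given.

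**The case against.** The strongest reply is that the article never calls the comparison unadjusted. Covariates and stratum terms are commonly left to a full protocol or analysis plan, and regressing change on treatment, baseline and procedure gives the same treatment estimate and residual variance as ANCOVA on the follow-up value. This stands as a limit: a reader might infer that the plan rules out or deliberately ignores baseline, but the text is only silent. It does not remove the point, because the change score is a stated choice and the only quantity named.

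Second, the effect on the next trial is conditional. The section says only that the comparison is to inform sample size. Oversizing needs the SD of change to be carried forward, the later trial to be analysed by ANCOVA, and a continuous outcome to drive its size. If that trial also analysed change, the SD of change would be the matching input. The same pilot data can also supply the follow-up SD and the correlation. All of this stands.

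Third, the size is uncertain. It depends on an unstated rho and on equal SDs, it is negligible at high correlation, and over most of the range it is smaller than the sampling error in a pilot variance. This stands too, with one qualification: sampling error is random, whereas the mismatch between the SD of change and the ANCOVA residual SD is systematic and avoidable.

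**Conclusion.** The point holds as an improvement to a stated method. If analysed without adjustment, the change score has 1.54, 1.33, 1.18 and 1.05 times the ANCOVA variance at rho 0.3, 0.5, 0.7 and 0.9. For the pilot's own estimate the factors are about 1.45, 1.26, 1.12 and 0.99, so at N = 20 nothing is gained at very high correlation. These figures assume equal SDs and a rho that the document does not give.

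Two stronger readings are not supported. One is that the definitive trial will be too large by these factors; that follows only under the conditions set out above. The other is that the change-score comparison is biased. Under randomisation it is unbiased on average, and the shift in Step 4 is conditional on the baseline imbalance that happens to be observed.

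The primary aims of feasibility and acceptability are untouched. The argument also does not reach complications or length of stay, which have no baseline value, and no change is proposed for them.

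**What to change.** In the Statistical analysis section, replace the change-score comparison for the continuous secondary outcomes. For each outcome and follow-up time, model the follow-up value on treatment, baseline value and surgical procedure, and report the adjusted difference with its 95% confidence interval. Alongside it, report the follow-up SD, the baseline/follow-up correlation and the residual SD, each with an interval, and name these as the inputs to the definitive sample size. If adjustment is already intended, one sentence saying so, plus the list of summaries to carry forward, is enough.

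The cost is analysis wording and two model degrees of freedom (residual 20 − 4 = 16 instead of 18 with complete data). No new data or visits are needed.

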### Timeline

Based on the number of cytoreduction surgeries and pelvic exenterations conducted at RPAH each year and on our experience with recruitment rate in previous pelvic exenteration studies, it is expected that three participants be recruited per month, to complete recruitment in 7 months (total *n* = 20). The feasibility and acceptability (primary aims of the study) will be completed in 8 months and the final follow-up assessment and manuscript preparation will be completed in the following 3 months.

### Data integrity and privacy

Consenting patients will be allocated to a unique study identification number. The list that matches individual patients with study identification numbers will be kept secured by the study chief investigators in a separate file on a password-protected computer, which will be based on a secure server hosted by the Sydney Local Health District (SLHD) and supported by Information Management and Technology Division (IM&TD). Study data will be entered into a REDCap database with individuals identified by their study identification number (i.e. in re-identifiable format). Only the study coordinators and investigators will have access to these data. All hard copies of the assessment booklets will be kept in a locked filing cabinet in the locked Surgical Outcomes Research Centre (SOuRCe) office at RPAH. This cabinet can only be accessed by the research personal named in this application. These records will be kept for 15 years after conclusion of the study, in accordance with statutory requirements. At the end of the 15 years, all files, electronic and paper, will be destroyed as per SLHD policy. The chief investigator will be the custodian of the study data and will meet with the associate investigators on a monthly basis to monitor data management. The study chief investigator will adhere to a data-cleaning schedule and conduct regular data audits to ensure data integrity. Basic checks will be conducted to identify data entry errors and any errors identified in this process will be corrected. The chief investigator will manage all personal health information in accordance with the Health Records and Information Privacy Act 2002 (HRIP).

### Data and Safety Monitoring Board (DSMB)

A senior lecturer from the Discipline of Physiotherapy of The University of Sydney will be the principal independent member of the Data and Safety Monitoring Board (DSMB) and will monitor adverse events and adherence to the protocol at regular intervals to ensure the safety of participants. The frequency of DSMB meetings and the stopping rules for the study will be defined a priori in a charter, in consultation with the DSMB members and study investigators.

### Research codes of conduct

The trial will conform to the following guidelines and regulations: the Note for Guidance on Good Clinical Practice (GCP), the National Statement on Ethical Conduct in Human Research and the Australian Code for the Responsible Conduct of Research.

## Discussion

This manuscript presents the protocol of a pilot randomised controlled trial evaluating the feasibility and acceptability of a pre-operative exercise programme for individuals undergoing surgery for cytoreductive surgery and pelvic exenteration. This pilot study will provide preliminary data that will be used to inform the design and methodology of a future phase-3 randomised controlled trial investigating the effectiveness of pre-operative exercise programme on patients’ post-operative complication rates, length of hospital stay, function and quality of life outcomes for patients undergoing major cancer surgery. The results of PEPA Trial has the potential to provide robust data to guide clinical decision-making.

A limitation of the pilot study is that patients cannot be blinded to the intervention, which could bias the self-reported outcome measures (secondary aim). However, measures will be taken to minimise bias. The physiotherapist performing the physical assessment and the treating surgeons will be blinded to group allocation. Furthermore, patients will be instructed not to reveal the group to which they were allocated.

## Trial status

The PEPA feasibility and acceptability trial recruited and randomised the first patient on 10 October 2017. The completion (follow-up of all patients) of the PEPA Trial is planned for June 2018. The results are expected to be submitted for publication at the end of 2018.

## Abbreviations

6MWT: Six-minute Walk Test
ACCP: American College of Chest Physicians
ANZCTR: Australian New Zealand Clinical Trials Registry
ATS: American Thoracic Society
CONSORT: CONsolidated Standards of Reporting Trials
CPET: Cardiopulmonary Exercise Test
DSMB: Data and Safety Monitoring Board
GCP: Good Clinical Practice
HRIP: Health Records and Information Privacy Act
IM&TD: Information Management and Technology Division
IPAQ-SF: International Physical Activity Questionnaire-Short Form
MET: Metabolic equivalent
PEPA: Pre-operative Physical Activity Trial
PESQI: Pelvic Exenteration Surgery Quality and Improvement
PREMIER: Peritonectomy Surgical Research Programme
REDCap: Research Electronic Data Capture
RPAH: Royal Prince Alfred Hospital
SF-36: Short Form 36
SLHD: Sydney Local Health District
SOuRCe: Surgical Outcomes Research Centre
SPIRIT: Standard Protocol Items: Recommendations for Interventional Trials
VO_2_ max: Maximal oxygen uptake
